### Operational hypotheses

The hypotheses being tested by the experiments described in this Study Protocol are as follows:

Experiment A: changes in conscious experience manifest earlier in the active than the passive condition, as measured by behavioural responses;

Experiment B: backward masking can preclude changes in conscious experience in the passive condition but not (as much) in the active condition.

These hypotheses stem from the putative role of active inference to confirm the sensory input expected following action (as described in the Introduction). Active sampling should promote faster resolution of uncertainty, engendering earlier perceptual inference. These hypotheses can be expressed in terms of the following predictions about the patterns of data we expect to observe in each experiment:

1]*Subjective report of reappearance of peripheral stimuli will occur after a shorter delay following subjective disappearance in the active vs. the passive condition of Experiment A* (see Table 1).2]*The psychophysical reappearance threshold for the radius of the masking boundary (once eye gaze is inside this invisible circular boundary the stimulus is masked) will be higher ; i.e., a larger radius in the active vs. the passive condition of Experiment B* (see Table 2).

**Table 1 pone.0328836.t001:** Predictions about the effect of active (vs. passive) sampling on target time-to-reappearance in Experiment A.

Theory	Decrease	No change	Increase	Confidence
IIT	X	X		Low
NREP	X	X		Medium
AI	X			High

**Table 2 pone.0328836.t002:** Predictions about the effect of active (vs. passive) sampling on mask onset boundary distance in Experiment B.

Theory	Decrease	No change	Increase	Confidence
IIT		X	X	Low
NREP		X	X	Medium
AI			X	High

Each of the other theories considered in the adversarial collaboration, IIT and NREP, offer different predictions to these, which also differ in their degree of confidence:

IIT is consistent with both manipulations (active or passive target sampling) quickly breaking suppression, by changing visual cortex state. Motor involvement (active) may be enough to tip the balance towards breaking suppression more easily, for a small difference in time to reappearance and/or masking boundary. Thus, for Experiment A (see Table 1), IIT predicts either decrease or no change, with low confidence; for Experiment B (see Table 2), IIT predicts either increase or no change, with low confidence.

NREP is compatible with motor movement conveying arousing/attentional effects (other than via active inference), which may facilitate early detection. For instance, motor activity can profoundly stimulate V1 firing activity, and motor-associated arousal may help to detect stimuli at greater distance from foveation point. Thus, for Experiment A (see Table 1), NREP predicts either decrease or no change, with medium confidence; for Experiment B (see Table 2), NREP predicts increase or no change, with medium confidence.

In addition to the two main hypotheses, we also predict the following, based on AI-C, which is not part of the adversarial collaboration and thus do not elicit predictions from the competing theories:

3)
*In Experiment B target stimuli will be discriminated more accurately in active vs. passive trials given the same frequency of reappearance.*
4)
*In Experiment B confidence in target discrimination will be higher in active vs. passive trials given the same frequency of reappearance.*

In the setting of the overall adversarial collaboration (TWCF ARC INTREPID), these sets of predictions will be considered in conjunction with predictions from all theories on three main experiments, in total. The aspiration is that this total set of findings from all experiments will strongly distinguish among these three theories (even if individual experiments are not able to strongly distinguish them). Table 3 illustrates some of the main predictions and confidences of each theory for selected, key parameters for each experiment, with Experiment 3 being described in this study protocol (for full details, please see the preregistration).

**Table 3 pone.0328836.t003:** Illustration of predictions and confidences for each theory about each consortium experiment (for selected, key parameters); for the full prediction tables and specification of the parameters, please consult the INTREPID preregistration.

Experiment	IIT	NREP	AI-C
1	Confirm prediction, high confidence	Predict no change, high confidence	Predict no change, medium confidence
2	Confirm prediction, medium confidence	Confirm prediction or predict no change, high confidence	Predict no change, medium confidence
3	Confirm prediction or predict no difference, low confidence	Confirm prediction or predict no difference, medium confidence	Confirm prediction, high confidence

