### Current study

Here, we describe a set of two experiments that form one of four Study Protocols (to be published separately), each of which is developed based on predictions of one of three major consciousness theories being tested in this adversarial collaboration (AI-C, IIT, and NREP).

As described above, the test of AI-C’s hypothesis proceeds by curtailing active inference in one, ‘passive’ condition, and contrasting that with an ‘active’ condition in which active inference leads to the selection of a policy of action with high expected information gain, with the prediction being that the active condition facilitates conscious awareness of the target. We will pursue this idea in a motion-induced blindness (MIB) paradigm, where a stationary peripheral target is rendered invisible due to the motion of a global pattern. We will contrast active sampling (via overt eye movement) with passive sampling (with eyes remaining at fixation) where, crucially, participants are exposed to identical visual input and retinal activation, and other task, attentional and expectation-related factors are kept constant. To assess the key prediction from AI-C that changes in conscious content will systematically occur earlier in the active condition, post hoc reports will assess whether the passively processed changes to sensory input are perceived later than the actively sampled changes.

In this study, we employ two experiments designed to assess these MIB active-passive differences (For more specific operationalised predictions relevant to the three theories considered in the adversarial collaboration (IIT, AI-C, NREP), see the section Operational Hypotheses below):

*Experiment A: Do changes in conscious experience occur earlier in the active than the passive condition?* This experiment will test whether the duration of MIB differs across the active and passive conditions. If there is no difference between conditions, or if MIB persists longer in the active condition, then that is strong evidence against AI-C. If MIB persists for longer in the passive condition, this would predominantly support AI-C.

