*Main experiment*. Following the successful completion of training and practice trials, participants will be reminded (via diagram) how to complete active and passive trials before the main experiment begins. Participants will be informed that a cue in the active trial will allow them to move their eyes to look at the location where the target was previously seen; in contrast, in the passive trials the cue is an instruction to maintain fixation. During each experimental trial, the participant will be initially required to perform an uninterrupted fixation on a central dot for at least 1.5 seconds before responses can be given. If the participant is unable to maintain eye gaze on the target for more than 1.5 seconds, they will not be able to complete the trial. If the participant looks at the peripheral target stimulus during this time period, the trial will automatically end (and will not be counted as a valid trial). The participant will then be asked to press a button when the peripheral target stimulus entirely disappears; following this response, after a short delay (randomly jittered between 500ms-1000ms) a cue will be given to signal the next phase by flashing a different colour of the central fixation. In the active trial block, after the cue, the participant will be asked to look to the target location. In the passive block, participants will be told to maintain central fixation while the entire visual display (including the rotating grid) moves in relation to the fixation cross to eventually position, in an exact replay, the stimulus as it was in a randomly selected trial from the active block. Crucially, in this version of the experiment participants will be asked to respond as soon as they become aware of the target, thereby generating an estimate of the time to reappearance.

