**Fig 3 pone.0328836.g003:**
[figure not shown]
An example resolved LMM analysis decision tree for experiment A & B. Here solid lines denote variables to be considered and grey boxes (dotted lines) denote decision criteria. Note: 1) Crossed out options are for example only, all options are available in real analysis tree. 2) For display purposes only included variables are written in full but variable selection at each level includes the same forks. 3) The third level criteria uses ascending steps to decide model variable inclusion. 4) Top of the tree denotes the basic model.

Trials will be rejected if:

1)any button press response is made < 3 seconds following the start of the trial2)time to reappearance is reported < 250 ms following the cue.3)time to reappearance is reported > 1 second following the cue.

**2. Eye-tracking.** Binocular gaze and pupillary response data for the experiment will be sampled at a frequency of 1000 Hz using a desk mounted SR Research Eyelink 1000 system (35 mm lens). Testing will be conducted in a sound attenuated room and display luminance will be matched across recording sites (Melbourne and Jena) using luminance measures taken from the four screen quadrants, taking into account room lighting. Participants will be seated with their head stabilised on a chin rest mounted 105.3 cm from the stimulus presentation screen and ~55 cm from the eye-tracking camera to the eye. At the start of the experiment a nine-point calibration and nine-point validation will be conducted. An additional validation will be performed at the start of each block. If any inter-block validation is not considered ‘good’ (worst point error < 1.5°, average error < 1.0°), the initial calibration and block validation will be repeated.

***Passive condition, eye-movement replay.*** The replay data processing must be completed within the inter-block period and has therefore been kept relatively streamlined to prevent additional computation time:

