1)Replay periods are epoched using a window extending from the initialization of the cue to the first fixation on the target stimulus.2)Any values outside of the boundaries of the screen are removed, and eyeblink periods must be linearly interpolated between points in order to maintain a smooth replay. Any datapoint more than 1.5° of visual angle away from the linear path from fixation to target will not be considered in the replay. Any datapoint more than 1.5° away from the previous data point is considered an error and will not be considered in the replay.3)Any trials containing poor signals (i.e., missing more than 20% of sample points in both eyes; [41]) will not be selected for replay. For replays that meet this standard all non-included samples will be linearly interpolated. To ensure equal numbers of active and passive trials, active trials may be used in replays additional times after running through all available replays. The replay path corresponding with the target stimuli will be used for replay if available, but the path trajectory will be transformed across randomly selected polar angles.

***Analysis.*** The following pre-processing steps describe the post-experiment analysis of eye tracking data for use in trial validation, eye-blink, microsaccade and pupillometry measures:

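### Experiment A's prediction times reappearance from the disappearance report, while the rejection rules and the replay time it from the cue; the prediction's clock adds a random 500–1000 ms delay to every outcome value

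*Protocol article*

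**What the plan says.** Two places start the clock at disappearance. Under Operational hypotheses, prediction 1 says that the reappearance report "will occur after a shorter delay following subjective disappearance in the active vs. the passive condition". Under Current study, the purpose of Experiment A is put as: "This experiment will test whether the duration of MIB differs across the active and passive conditions".

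Two places start it at the cue. The trial rejection rules (Data collection procedures, Behavioural Data) drop a trial if "time to reappearance is reported < 250 ms following the cue" or if "time to reappearance is reported > 1 second following the cue". The first step of the eye-movement replay reads: "Replay periods are epoched using a window extending from the initialization of the cue to the first fixation on the target stimulus".

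The two origins are not the same moment. The Main experiment paragraph of Experiment A says that once disappearance is reported, "after a short delay (randomly jittered between 500ms-1000ms) a cue will be given to signal the next phase".

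Table 1 names the outcome as time to reappearance and gives no origin. The Planned analyses section does not say which interval is the dependent variable. The Behavioural Data section does record timestamps for both the disappearance response and the cue.

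**The concern.** Prediction 1 is one of the article's two main hypotheses, and its outcome has two starting points. The choice matters for three reasons.

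- **Precision.** The delay before the cue is set by the computer and has nothing to do with the hypothesis. On the prediction's clock it is part of every outcome value. The article treats a finding of no difference as strong evidence against the active inference theory, while the two rival theories both allow no change. Avoidable noise therefore bears on how the theories are judged.
- **Matching.** The replay reproduces the active trial from the cue onward, so the cue is where the matched stimulation begins. The interval before it carries no part of the manipulation.
- **Consistency between sites.** Each laboratory develops and runs its own pipeline (Status and timeline). With two origins in the text, the two could in good faith compute different outcomes.

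**Working it through.** **The plan's own figure.** The sample size section adopts 55 participants for at least 80% power at partial eta squared 0.13. For a two-condition within-subject contrast, f² = 0.13/0.87 = 0.1494. With noncentrality 55 × 0.1494 = 8.22, 1 and 54 degrees of freedom and a two-sided 5% level (assumed, as the article states none), power is 80.4%. The figure reproduces, with almost no margin above 80%.

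**Inputs from the article.** Delay 500–1000 ms; accepted response range 250–1000 ms after the cue; 55 participants; 72 trials per condition. The same paragraph also mentions 144 trials of each type, so both counts are worked.

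**Inputs assumed.** The delay is uniform and independent of the cue-locked response time. The trial SD s of the cue-locked time is 150–250 ms. The SD τ of individual active-passive effects is 30–100 ms. Power on the cue clock is exactly 80%.

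**Step 1: the delay.** Mean = (500 + 1000)/2 = 750 ms. Variance = 500²/12 = 20,833 ms², so SD = 144.3 ms. On the disappearance clock the accepted range of 250–1000 ms becomes 250 + 500 = 750 ms to 1000 + 1000 = 2000 ms.

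**Step 2: trial variance.** The increase is 20,833/s². At s = 150 it is 20,833/22,500 = 93%. At s = 250 it is 20,833/62,500 = 33%.

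**Step 3: bias.** The delay is described identically for both conditions, so its 750 ms mean cancels in the active-minus-passive difference. The expected raw difference is the same on either clock.

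**Step 4: each participant's difference.** With K trials per condition the variance is τ² + 2s²/K on the cue clock, and τ² + 2s²/K + 2 × 20,833/K on the disappearance clock. The added term is 578.7 ms² (SD 24.1 ms) for K = 72 and 289.4 ms² (SD 17.0 ms) for K = 144.

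**Step 5: power.** With 55 participants, 80% power corresponds to a noncentrality of 2.853 in the paired t test. On the disappearance clock this is multiplied by the square root of the ratio of the two variances in step 4.

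| K | τ (ms) | s (ms) | Variance, cue clock | Variance, disappearance clock | Noncentrality | Power |
|---|---|---|---|---|---|---|
| 72 | 30 | 150 | 1525.0 | 2103.7 | 2.429 | 66.5% |
| 72 | 100 | 250 | 11,736.1 | 12,314.8 | 2.785 | 78.1% |
| 144 | 30 | 150 | 1212.5 | 1501.9 | 2.563 | 71.1% |
| 144 | 100 | 250 | 10,868.1 | 11,157.4 | 2.815 | 79.0% |

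These are the extremes of the assumed ranges: roughly 67–78% with 72 trials and 71–79% with 144.

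**Step 6: relative effects.** The origin also changes effects on a proportional scale. With an assumed cue-locked mean of 600 ms, a 50 ms difference is 50/600 = 8.3% on the cue clock and 50/1350 = 3.7% on the disappearance clock. The article chooses the link function from the data, so this could matter if a log-type link is used.

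**The case against.** The strongest reply is that the article has only one operational definition. The only numerical limits on time to reappearance are counted from the cue, Table 1 uses the same term, and the eye-tracking epochs also follow the cue or first fixation. On that view prediction 1 merely describes an order of events: disappearance, then reappearance. The article also refers readers to the preregistration for its full parameter specification, and it plans shared analysis principles under committee oversight. Either could settle the clock, and neither can be checked here.

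Much of this stands. It supports the cue as the better choice and makes a mismatch in practice less likely. It does not remove the conflict: prediction 1 names a starting point for the delay, the purpose of Experiment A is worded to match, and no sentence in the article reconciles them with the cue.

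Three stronger readings are tempting, and the article does not support them.

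- **That the comparison is biased.** It is not: the delay has the same described distribution in both conditions.
- **That power will be lost.** The loss arises only if the disappearance clock is used and the logged delay is neither subtracted nor modelled. The analysis section already allows covariates for sources of noise.
- **That the two laboratories will analyse different endpoints.** This is only a possibility. Separate pipelines are a deliberate safeguard.

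**Conclusion.** The point holds as a conflict over the time origin of a main outcome, with a cost in precision. Read literally, prediction 1 adds noise with an SD of about 144 ms to each trial value and leaves the expected raw difference unchanged. The power figures are illustrative: the loss runs from about 1 to about 13 percentage points and is small where individual effects vary widely. They rest on a uniform delay, the assumed SDs, a two-sided 5% level and 80% power on the cue clock. The article takes 55 participants from another study rather than deriving that number for this outcome. The sample size itself is not called into question. The conflict merits correction because the prediction fixes one clock, the processing rules use another, and the cue clock avoids the loss whatever the true SDs are.

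**What to change.** State in prediction 1 and Table 1, and for both laboratories' pipelines, that the Experiment A outcome is the time from cue onset to the reappearance press. Bring the wording about the duration of motion-induced blindness under Current study into line. If a disappearance-based measure is also reported, make it secondary and subtract the logged delay or include it as a covariate.

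The cost is administrative. The design is preregistered and data collection is under way, so the change needs agreement from both sites and the three theory leads and a timestamped entry in the preregistration record. Both timestamps are already logged, so no new data are needed.

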### Experiment B: MIB target masking threshold for reappearance, content discrimination and confidence

**Design, stimuli, and procedure.** Experiment B repeats the design of Experiment A with the (i) inclusion of a backwards masking procedure and (ii) the elicitation of stimulus discrimination and confidence reports. Stimulus masking will be initiated when the centre of gaze crosses an invisible circular boundary around the target stimulus. Whilst in the active condition the boundary will remain stationary around the target stimulus, in the passive condition the boundary will track the stimulus as it moves (via replay) towards the centre of the screen (see Fig 2 [right]). The radius of the circular boundary will be iteratively expanded or contracted using an adaptive staircase procedure designed to identify the threshold for conscious perception of the stimulus (see Fig 2 [left]). Additionally, in experiment B instead of immediately reporting reappearance, at the completion of the trial participants will be asked whether the stimulus reappeared.

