*Practice Experiment.* The practice phase will replicate that of Experiment A, with additional instruction about the stimulus discrimination task, the masking of the stimuli when making the saccades and the choice screen at the end of the trials. Participants will receive warnings if they incorrectly select foils during the stimulus discrimination task in order to encourage correct task engagement.

*Main experiment*. The main experiment follows the same general procedure outlined for Experiment A, with the additional inclusion of the backward masking, stimulus discrimination, and confidence report procedures. During active trials, participants will be cued to saccade to the target location after reporting its disappearance. When eye gaze crosses an invisible masking boundary, the stimulus will disappear. The precise radius of this boundary will be adjusted on a trial-by-trial basis (see Fig 2), such that the boundary will be expanded around the stimulus (i.e., masking is initiated earlier in the saccade) following trials in which the stimulus was reported to reappear, or the radius will be reduced around the stimulus (i.e., masking is initiated later in the saccade) following trials in which the stimulus was reported to have not reappeared. The number and length of trials will be identical with Experiment A.

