### Data collection procedures

**1. Behavioural Data.** Participants will use a key press to indicate the disappearance of the peripheral targets. A timestamp will be set when the disappearance response is given, when the cue is initiated, and when the stimuli are actively or passively foveated. This will allow precise extraction of replay gaze trajectories from the onset of fixation. In Experiment A, participants will be required to press the spacebar as soon as they become aware of the stimulus; in Experiment B, participants will be asked to give a forced binary choice after the trial to report whether stimulus reappeared. The invisible boundary that initiates the mask will be expanded if they report reappearance and contracted if they do not. If a reappearance is reported participants will be asked a subsequent question about the identity of the stimulus. The participant can choose a present identity or a ‘no match’ option. In 50% of the trials the identity shown in the trial will not match that presented in this post-trial question, allowing us to compute signal detection theoretic measures. Participant choice will also yield a confidence measure based on their click location (see Fig 3). To analyse the data we will fit linear mixed-effects models on the psychophysical awareness threshold. This will be quantified as the invisible boundary radius at which there is a 50% reappearance report rate under the model, with Active vs. Passive condition included as a predictor, potentially including and potential nuisance variables as covariates. Similar models will be fit to analyse signal detection theoretic measures of target discrimination and decision confidence.

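### Predictions 3 and 4 assume equal reappearance frequency, but the staircase delivers that only after it converges, so pooling all yes-trials can favour the active condition

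*Protocol article*

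**What the plan says.** Four parts of the protocol article bear on this point.

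- **Predictions 3 and 4** (Operational hypotheses): "target stimuli will be discriminated more accurately in active vs. passive trials given the same frequency of reappearance", and "confidence in target discrimination will be higher in active vs. passive trials given the same frequency of reappearance". The article places both outside the adversarial comparison.
- **Prediction 2** (same section): the threshold for the masking boundary will be "a larger radius in the active vs. the passive condition of Experiment B".
- **Staircase** (Experiment B; Data collection procedures): "The radius of the circular boundary will be iteratively expanded or contracted using an adaptive staircase procedure", and the direction is fixed: "The invisible boundary that initiates the mask will be expanded if they report reappearance and contracted if they do not". The threshold is "the invisible boundary radius at which there is a 50% reappearance report rate under the model".
- **When discrimination and confidence are collected** (Data collection procedures): "If a reappearance is reported participants will be asked a subsequent question about the identity of the stimulus". Confidence is read from the same response, so neither measure exists on no-trials.

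For discrimination and confidence the article says only that models similar to the threshold model will be fitted. The trial-rejection rules concern response times, fixation and signal quality. None sets aside the run-in of the staircase.

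**The concern.** The comparison in predictions 3 and 4 is conditional on equal reappearance frequency. The yes-trials that the experiment collects do not meet that condition over the whole run if prediction 2 is true. The boundary moves outward only through yes-responses "following trials in which the stimulus was reported to reappear", so a condition that ends at a larger radius must have had more of them, given the same start and step.

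The surplus need not be neutral. If the run starts below the active threshold, it consists of trials with a small radius, in which masking comes late and the face stays visible longest. Identification and confidence should be best on those trials. If all yes-trials are pooled, the active condition can look better on both measures although perception at a matched frequency is identical. The error is then in the predicted direction.

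**Working it through.** **Inputs from the article.** The expand/contract rule; the 50% threshold; discrimination asked only after a yes; N = 72 or 144 trials per condition (the Experiment A design paragraph gives both figures, and Experiment B takes its trial number from Experiment A); 55 participants.

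**Assumptions, not in the article.** One staircase per condition; common starting radius; fixed step of 0.1, 0.25 or 0.5 deg; thresholds of 4 deg (active) and 3 deg (passive); logistic psychometric function with slope 0.6 deg; accuracy rising from 50% to 100% and depending only on distance from the condition's own threshold. There is therefore no true active advantage at matched frequency.

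**Step 1: the article's 50%.** With yes-probability p, the expected move per trial is step × [p − (1 − p)] = step × (2p − 1). This is zero at p = 0.5, so each condition settles at 50% whatever its threshold radius.

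**Step 2: yes-rates over all trials.** Without clipping at the range limits:

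- yes − no = (R_end − R_start)/step, and yes + no = N
- yes/N = 1/2 + (R_end − R_start)/(2 × step × N)
- active minus passive rate = D/(2 × step × N), that is D/(2 × step) extra yes-trials

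With D = 4 − 3 = 1 deg:

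| Step (deg) | Extra yes-trials | N = 72 | N = 144 |
|---|---|---|---|
| 0.1 | 5 | 6.9 points | 3.5 points |
| 0.25 | 2 | 2.8 points | 1.4 points |
| 0.5 | 1 | 1.4 points | 0.7 points |

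Simulation (10,000 runs per setting) agrees. In the second half of the run the gap is 0 to 0.2 points at N = 144. At N = 72 it is about 0 for steps of 0.25 deg or more, and up to 3.8 points at 0.1 deg with a distant start.

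**Step 3: spurious accuracy advantage when all yes-trials are pooled** (20,000 runs per setting for fixed steps; points in favour of active).

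| Setting | Advantage |
|---|---|
| N = 72, start 0.5 to 2 deg, step 0.5 / 0.25 / 0.1 | about 1.0 / 1.9 to 2.0 / 3.5 to 4.3 |
| N = 72, start 3.5 deg, steps 0.5 to 0.1 | 0.6 to 3.3 |
| N = 72, start 7 deg | about 0.1; 1.3 at step 0.1 |
| N = 144, low start | 0.5 to 2.5 |
| Steps halving from four times the final value to 0.25–0.5 deg | at most 0.7 (N = 72), at most 0.3 (N = 144) |

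**Step 4: what such a bias could do to a test.** With about 36 yes-trials per condition (half of 72), accuracy of 0.75 and 55 participants, the standard error of the difference is √(2 × 0.75 × 0.25/36/55) = 0.0138, or 1.4 points. The one-sided error rate is 1 − Φ(1.96 − bias/SE). Biases of 0.8, 1.5 and 2.8 points turn a nominal 2.5% into about 8%, 19% and 53%. These are upper-end values: the standard error is purely binomial, so variation between participants would lower them. They also refer to raw accuracy at N = 72, whereas the article plans signal detection measures.

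**Step 5: which trials to drop.** Dropping the first third cuts the bias to about 0.1 points or less for steps of 0.25 deg or more, but at 0.1 deg and N = 72 the run may still not have converged. Starting after the fourth reversal (N = 72, step 0.1, start 3.5 deg) left 1.8 of 3.2 points in one simulation and 2.1 of 3.4 in another. A fixed count is not a safe criterion.

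**The case against.** The staircase is itself the matching device. A reader might infer that the frequency match fails whenever prediction 2 is true. The article does not support that: Step 1 shows each condition going to 50%, and the imbalance is a start-up transient.

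The clause about equal frequency can also be read as a comparison at the modelled 50% point. The article defines the threshold that way and promises similar models for discrimination and confidence. Starting radius, step rule and run-in are details that a condensed article may leave to the preregistration or an analysis plan. The article calls the staircase only adaptive. If its steps shrink, the identity does not apply and the bias is small. Practice trials might also inform the start.

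Most of this stands. It limits the size of the problem and rules out any claim that the bias must occur. What remains is that the article states a matching condition, collects the measures on every yes-trial from the first one on, lists trial-rejection rules that leave the run-in in, and does not tie the comparison to the 50% point or to converged trials.

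A second stronger reading is that one staircase serves both conditions, since the Current study section speaks of applying one masking setting to both. Simulated that way, the yes-rate gap would persist at about 2 to 59 points. The article does not say the staircase is shared, and the mechanism would differ, because the two conditions would then have no separate end radii. No conclusion is drawn from it here.

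**Conclusion.** The concern holds in limited form. Under per-condition staircases with a common start and a fixed step, using all trials does not give the equal frequency on which predictions 3 and 4 rest, and with a low or middle start the error favours the active condition. Its size depends on settings the article does not give: near nil with a high start and steps of 0.25 deg or more, or with steps shrinking to 0.5 deg; about 1 to 4 accuracy points with 72 trials, fixed steps of 0.1 to 0.5 deg and a low start; roughly half to two thirds of that with 144 trials. The inflation of false-positive findings is correspondingly uncertain. Prediction 2 and the adversarial comparison are not affected by this.

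**What to change.** State that predictions 3 and 4 are tested at matched frequency, in one of two ways:

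- model discrimination and confidence against radius and evaluate them at each condition's fitted 50% radius, which the threshold model already supplies; or
- use only post-convergence trials in each condition, with convergence shown by active and passive reappearance rates near 50% in the analysed trials, and not by a reversal count alone.

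Either way, report the reappearance rate by condition for the trials analysed, so that equal frequency is demonstrated. Keep all trials for the threshold fit.

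The cost is one analysis rule and no new data. The second option uses fewer trials and the first loses a little precision, in both cases only for two predictions outside the adversarial comparison.
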